
In summary, rehabilitation programs can contribute to a reduction in physical, neurocognitive, and psychological restrictions, thereby stabilizing or even increasing patients' physical and mental performance after recovery from COVID-19. This is a prerequisite for maintaining the ability to work on a long-term basis after COVID-19, which is associated with economic costs. Considering the diverse and variable symptomatology, especially the associated physical limitations, social and occupational participation disorders are to be expected. However, there is currently no research focusing on the nature and extent of returning to work after COVID-19. Consequently, COVID-19 is associated with great challenges for the healthcare systems worldwide. In addition to acute patient treatment, long-term care of COVID-19 patients will be necessary after the acute phase due to illness-related impairments. However, based on the lack of longitudinal data and results, the sustainability of rehabilitation effects could not yet be confirmed. Indeed, since patients with severe to critical COVID-19 seem to benefit from rehabilitation soon after the acute phase of infection, rehabilitation programs are recommended for all hospitalized COVID-19 patients to avoid long-term adverse health outcomes (53, 60). However, inpatient rehabilitation programs should not only be offered directly after hospitalization and temporary discharge, but also weeks and months after the acute phase of COVID-19, depending on the existing symptoms of post-COVID (51). Together with the case control management of health services, rehabilitation should be provided to regain functionality in everyday and workday activities.

In this context, this study examines the following main research questions:

- What are the long-term outcomes of patients following OAC after undergoing an intensive rehabilitation program? Of particular interest are patients' physical capacity, psychological and cognitive well-being, and ability to work.- Are age, gender, previous diseases, and employment at the time of exposure, as well as comorbidities associated with long-term outcomes of OAC of patients' physical capacity, psychological and cognitive well-being, and ability to work?- Are physical capacity and psychological and/or cognitive well-being predictors for ability to work or return-to-work?

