## Methods and Analysis

### Study Design

The current study is an observational cohort study executed at the BG Hospital for Occupational Disease in Bad Reichenhall, Germany and at the Chemnitz University of Technology (TU Chemnitz), Germany. After successful screening for study eligibility, participants will complete medical, diagnostic, respiratory, neurocognitive, psychological, and physical performance measurements at four different time points (T1-T4). In addition to these, measurements using an activity sensor and a standardized interview for mental disorders will be performed at three different time points (see Figure 1). Data from the participants will be recorded over 21 months at the beginning (T1) and the end (T2) of inpatient rehabilitation. The follow-up time points 6 (T3) and 12 (T4) months after the beginning of inpatient rehabilitation consist of three examination days and will also be conducted by trained project staff at the BG Hospital for Occupational Disease Bad Reichenhall and at the TU Chemnitz.

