#### Neurocognitive Measurements

##### Montreal Cognitive Assessment

Cognitive performance will be assessed using the MoCA as the primary outcome in this area of the investigation. The MoCa is a short screening tool to identify cognitive impairments in patients, i.e., in memory, attention, or executive functions. Following the recommendations by Nasreddine et al. (65), participants who reach a MoCA score between 30 and 26 points will be classified as cognitively healthy, whereas individuals with a MoCA score of 25 or lower will be considered cognitively impaired (65). To avoid learning effects, different versions of the MoCA will be implemented at different measurements points: Version 1 at T1, Version 2 at T2, Version 3 at T3, and again Version 1 at T4.

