##### 6-Minute Walk Test

The 6MWT, as the primary outcome in this area of the investigation, was chosen to assess functional exercise capacity. This test requires a walkway that is at least a 30m long. The walking course will be marked every 2 m. A cone will be placed on the ground to mark the turning points. The test coordinator will use a stopwatch to inform the participant when 6 min are over. Before starting the test, the participant has to sit on a chair close to the course for at least 10 min. The participant will be instructed to avoid talking while walking (87, 88). The outcome measure of the 6MWT is the distance in meters covered by the participant within 6 min. The 6MWT will be combined with a blood-gas analysis (Cobas b221, Roche Diagnostics intern., Rotkreuz, Switzerland) to provide information about the gas distribution of oxygen and carbon dioxide, the pH level, and the acid-base balance (89).

Finally, gait velocity of the first 10 meters of the 6MWT will be recorded to assess functional mobility, gait, and vestibular functions. The test coordinator will measure the time the participant requires to walk 10 meters, so that the velocity in seconds per meter can be calculated (90). Gait abnormalities will also be observed.

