To detect the outcomes over time, differences between 2 dependent samples (T1 and T2) will be analyzed. The minimal clinically important difference between two measurement time points is 30 meters for the 6-minute-walking-distance (88). According to experience from our own studies on physical performance in patients with occupational respiratory diseases, standard deviations between 80 and 100 m are to be expected (100, 101). Assuming a standard deviation of 100 m (due to heterogeneity of the sample) and an expected effect size of d = 0.3, 71 data sets are required with a power of 80% and significance level of 5%.

While a drop-out rate of 25% is expected during the study period of 21 months, a total sample size of at least 115 patients will be included.

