### Statistical Analysis

IBM SPSS Statistics Version 28 and AMOS Version 28 (IBM Corp., Armork, NY, USA) will be used for all statistical analyses.

First, to determine the existing outcomes of COVID-19 on physical capacity, psychological and cognitive well-being, and the ability to work at the beginning of inpatient rehabilitation (T1), the population will be descriptively characterized by all measured outcomes. Data from participants at the end of inpatient rehabilitation (T2) and at the follow-up time points (T3, T4) will be analyzed to further evaluate the long-term outcomes of patients with COVID-19 undergoing an intensive rehabilitation in terms of physical capacity, psychological and cognitive well-being, and the ability to work. Normal distribution and homoscedasticity of the sample will be realized using the paired *T*-test or Wilcoxon-test. Depending on the feasibility for the current population, group differences (e.g., age, gender, pre-existing conditions, comorbidities, current employment) in the long-term effects of COVID-19 on physical capacity, psychological and cognitive well-being, and the ability to work will be analyzed separately for the different time points (T1, T2, T3, T4) using different statistical methods as follows. Taking into account the number and size of groups, normal distribution and homoscedasticity of the sample, parametric or non-parametric statistical methods such as the *T*-test, Mann-Whitney *U*-test, ANOVA, or the Kruskal Wallis test will be used. To evaluate the associations between the different outcome measures of physical capacity, psychological and cognitive well-being, and ability to work, correlation analysis will be performed to measure the strength of the relationship between two variables, e.g., 6MGT and HADS-D or 6MGT and WAI. Depending on these results and current insights from the literature, multivariate and logistic regression analyses accounting for confounders such as age, gender, or comorbidities will be conducted to identify predictors or meditators of the long-term outcomes of COVID-19. For example, a logistic regression analysis will be used to examine the relationship between physical capacity, psychological and cognitive well-being and the dependent variable return to work 6 or 12 months after the start of inpatient rehabilitation. For all analyses, Bonferroni correction for multiple testing will be applied and statistical significance level will be set to *p* < 0.05. After inspecting the amount and pattern of missing data and outlier values, the most appropriate procedure for addressing both factors will be selected.

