
## Conclusion

Using the planned study protocol, long-term effects of OAC on physical capacity, mental health, and work ability will be assessed and described in detail. With a follow-up period of 12 months after the start of inpatient rehabilitation, the project makes an important contribution to the state of knowledge about the long-term effects of the disease. In addition, this study will present associations between physical capacity, mental health, and work ability, as well as the influence of age, gender, comorbidities, and occupation. Moreover, measures, occurring peculiarities, and the feasibility of the inpatient treatment procedure for patients with OAC will be documented. During and at the end of the project period, (interim) results and findings will be summarized in information brochures and presented at information events for the accident insurance institutions. When interpreting the results, it should be considered that the target group is a selective sample of patients with the diagnosis of COVID-19 as a recognized occupational disease or work-related accident. In Germany, the BG Hospital for Occupational Disease Bad Reichenhall is a clinic specialized in the treatment and rehabilitation of occupational diseases and consequently appropriate for the investigation of this sample group. A randomized, controlled study design cannot be applied in the context of the current research project. Since the progression of COVID-19 is acute and associated with direct health-related consequences, it is ethically and medically irresponsible to deny affected insured persons inpatient rehabilitation over a longer period. Nonetheless, the results of the current study will contribute to further developing recommendations for monitoring and coordinating targeted and tailored inpatient rehabilitation in the context of sustainable rehabilitation management for patients after COVID-19. This can help optimize the procedures and processes of post-COVID rehabilitation with the aim to improve the patients‘ physical and mental health, and to support individual occupational ability. Finally, the results will provide a basis for further research, such as the development of disease-specific, health-promoting, and rehabilitative strategies for the sustainable healthcare of patients with COVID-19.

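### The only sized change contrast is the inpatient stay (T1 to T2) at an unadjusted 5% level, so no sized contrast answers the 12-month question and the 80% power does not carry over to Bonferroni-corrected tests

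*Protocol article*

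**What the plan says.** The first main research question in the Introduction is "What are the long-term outcomes of patients following OAC after undergoing an intensive rehabilitation program". The Conclusion puts the study's value in the same place: "With a follow-up period of 12 months after the start of inpatient rehabilitation, the project makes an important contribution". Study Design sets T1 and T2 at the beginning and end of the inpatient program, which lasts at least 3 weeks, and adds "The follow-up time points 6 (T3) and 12 (T4) months after the beginning of inpatient rehabilitation".

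The Sample Size Calculation contains two calculations. One is a cross-sectional regression at the start of rehabilitation (92 data sets). The other is the only one about change: "To detect the outcomes over time, differences between 2 dependent samples (T1 and T2) will be analyzed". It takes 30 m as the minimal important difference on the 6-minute walk test (6MWT), a standard deviation of 100 m, d = 0.3, 80% power and a 5% level, and arrives at 71 data sets.

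Three outcomes are each called primary in their own area. For cognition: "Cognitive performance will be assessed using the MoCA as the primary outcome in this area of the investigation". For physical capacity: "The 6MWT, as the primary outcome in this area of the investigation, was chosen to assess functional exercise capacity". The Work Ability Index (WAI) has the same label under Measurements to Assess Work Ability.

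Statistical Analysis says "Data from participants at the end of inpatient rehabilitation (T2) and at the follow-up time points (T3, T4) will be analyzed" in order to evaluate long-term outcomes. It models "return to work 6 or 12 months after the start of inpatient rehabilitation" and applies Bonferroni to all analyses at 0.05. No section says which visit or contrast is the main one.

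**The concern.** T1-T2 describes what happens during a stay of a few weeks. It cannot say what remains at 6 or 12 months. If it is the only change that was sized, the study's first question has no contrast with a stated chance of being answered.

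The analysis section widens the gap. It places the discharge visit in the same sentence as the two follow-ups, and the return-to-work model leaves 6 or 12 months open. Three area-primary outcomes by three post-baseline visits give nine baseline contrasts, and none is marked as the main result.

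The sizing and the analysis also use different levels. The calculation spends the full 5% on one test, while the analysis promises Bonferroni throughout. A reader of the final report would see a stated 80% power that belongs neither to the question asked nor to the level at which the tests are run.

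**Working it through.** **Inputs from the protocol article.** d = 30/100 = 0.3; 80% power; 5% level; 25% drop-out; at least 115 patients; three area-primary outcomes (6MWT, MoCA, WAI); three post-baseline visits (T2, T3, T4).

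**Inputs that are assumptions.** d = 0.3 carries over from T1-T2 to T1-T4 and from 6MWT to MoCA and WAI; the full 25% drop-out applies; tests are two-sided unless stated.

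**1. Reproduce the plan's figures.** Paired t-test, noncentrality d × √n, n − 1 degrees of freedom:
- one-sided 5%, 80% power: n = 71, matching the plan;
- two-sided 5%: n = 90; with n = 71, two-sided power is 0.70.

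The regression (f² = 0.15, 5 predictors) gives 92, also matching. The total is 92 × 1.25 = 115, so the regression sets the enrolment and the paired calculation does not.

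**2. Completers.** 115 × 0.75 = 86.25, taken as 86. Noncentrality is 0.3 × √86 = 2.78.

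**3. Power per test with 86 completers.**

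| Tests sharing the 5% | Level per test | Power, two-sided | Power, one-sided | Completers for 80%, two-sided |
|---|---|---|---|---|
| 1 | 0.05 | 0.785 | 0.868 | 90 |
| 3 (T1-T4 for three primaries) | 0.05/3 = 0.0167 | 0.63 | 0.73 | 120 |
| 4 (adding one psychological measure) | 0.05/4 = 0.0125 | 0.59 | 0.69 | 128 |
| 9 (three primaries × T2, T3, T4) | 0.05/9 = 0.0056 | 0.48 | 0.58 | 150 |

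**4. Sensitivity to d.** If 100 m is the standard deviation at one visit, the standard deviation of the change is 100 × √(2(1 − r)), where r is the correlation between the two visits. d = 0.3 then corresponds to r = 0.5. The article does not give r.

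| r | d = 30/SD of change | n at 0.05, two-sided | n at 0.05/9, two-sided |
|---|---|---|---|
| 0.3 | 0.25 | 125 | 208 |
| 0.5 | 0.30 | 90 | 150 |
| 0.7 | 0.39 | 55 | 91 |
| 0.8 | 0.47 | 37 | 62 |

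At r = 0.8, 86 completers would be enough even over nine contrasts. At r = 0.5 or below they would not.

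**5. False positives under the plan's own Bonferroni rule.** Simulation under no change, assuming independent visit errors (so contrasts with T1 correlate 0.5) and between-outcome correlations from 0 to 0.8:
- Bonferroni over all nine contrasts: 0.034 to 0.046, about 0.042 at correlation 0.5;
- Bonferroni over the three visits of one outcome, error within that area: about 0.044;
- the same rule, with error pooled across the three areas: 0.09 to 0.13, 0.115 at correlation 0.5;
- only the three T1-T4 tests at 0.05/3: 0.035 to 0.049.

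**The case against.** The strongest reply is that this is a single-cohort, largely descriptive study. It has no control arm, and no section says that one significant contrast makes the study a success. A reader might infer that nine unranked contrasts let the authors claim opposite conclusions. The document does not support that: a gain at discharge that is lost by 12 months is a trajectory this cohort is set up to describe. Nor does it support an inference that errors go uncontrolled. Bonferroni is promised for all analyses, and it keeps the error below 5% over all nine contrasts or within each area. The excess appears only if error is pooled across areas that the article treats separately. This part of the reply stands.

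It is also fair that T1-T2 matters for another stated aim, recommendations for inpatient rehabilitation; that the Statistical Analysis section calls only T3 and T4 follow-up time points; and that the details of a Bonferroni family are commonly left to an analysis plan. The power figures borrow d = 0.3 for outcomes for which the article gives no effect size.

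None of this removes the mismatch. The article itself chose a contrast for outcomes over time, and that contrast is not the one its first question asks about. It also states the level for that contrast, and that level is not the one its analysis rule implies. Which visit answers a long-term question is part of the question and belongs in the protocol.

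**Conclusion.** The point holds as a mismatch between question, sizing and analysis. The long-term question has no sized contrast, and the stated 80% power applies to a short-term 6MWT change at an unadjusted 5%, one-sided as reproduced. If d = 0.3 is carried over to T1-T4 and to the other primaries, with 86 completers and two-sided tests, power per test is 0.48 across nine contrasts and 0.63 across three T1-T4 tests. These are illustrations: the result depends on the unstated correlation between visits, and a correlation of 0.8 would leave power adequate for 6MWT. The article should be corrected on this point. Because false positives are restrained by the Bonferroni rule, the cost is lost power and no designated main result, not an inflated claim.

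**What to change.** In Sample Size Calculation and Statistical Analysis:

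1. Name change from T1 to T4 as the main contrast for each area's primary outcome (6MWT, MoCA, WAI). Research question 1 also covers psychological well-being, so either add one named measure already collected, such as HADS-D, or state that this domain is secondary.
2. Apply Bonferroni or Holm to those T1-T4 tests only: 0.05/3, or 0.05/4 with a psychological measure.
3. Report T2 and T3 as supportive, with estimates and confidence intervals that describe the trajectory.
4. State that the existing paired calculation covers short-term 6MWT change at an unadjusted 5% only, or restate its power for T1-T4 at the corrected level, giving the sidedness and the standard deviation of the change.

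This is wording only and needs no new patients or measurements. The costs are that T1-T2 change is no longer confirmatory, that T4 probably has the fewest completers, and that the restated power may fall short of 80% (0.63 with three tests, 0.59 with four, on the assumptions above).

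### The 71 data sets for the paired T1–T2 walk-distance comparison follow only from an unstated one-sided test, and the 100 m behind them is not identified as an SD of change

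*Protocol article*

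**What the plan says.** The second part of the Sample Size Calculation section concerns change over time: "differences between 2 dependent samples (T1 and T2) will be analyzed". The difference to detect is 30 m: "The minimal clinically important difference between two measurement time points is 30 meters". For the variability, the article draws on the group's own studies of physical performance in occupational respiratory disease: "standard deviations between 80 and 100 m are to be expected". It then takes the upper end: "Assuming a standard deviation of 100 m (due to heterogeneity of the sample) and an expected effect size of d = 0.3". The result is "71 data sets are required with a power of 80% and significance level of 5" percent.

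The Statistical Analysis section names the paired t-test or the Wilcoxon test for this comparison ("will be realized using the paired *T*-test or Wilcoxon-test").

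The article does not state whether the test is one-sided or two-sided, whether 100 m is the SD of walking distance or of its change, or what T1–T2 correlation is assumed. The same section derives 92 data sets for a multiple regression and, with 25% drop-out, a total of at least 115 patients.

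**The concern.** Two things are unclear in one short calculation.

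The first is sidedness. A 5% level with no qualifier is normally read as two-sided, and nothing in the article says otherwise. If the test is two-sided, 71 is too small for the effect size the article itself states.

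The second is the SD. The effect size for a paired test is the mean change divided by the SD of the within-patient change. The article supports 100 m by the heterogeneity of the sample. That is a natural reason for a wide spread of distances across patients, and a less obvious reason for a wide spread of changes. If 100 m is the SD of distance, 30/100 is not the paired effect size unless the T1–T2 correlation happens to be 0.5.

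At stake is whether a reader can rely on the stated power for a 30 m change in the outcome that the article names as primary for physical performance.

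**Working it through.** **Inputs from the Sample Size Calculation section.** Difference 30 m; SD 100 m; d = 30/100 = 0.3; power 80%; significance level 5%; two dependent samples.

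**Method.** Exact power of the paired t-test: noncentral t with n − 1 degrees of freedom and noncentrality d·√n. The required n is the smallest one with power of at least 0.80.

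**Step 1: reproduce the stated figure at d = 0.3.**

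| Test | Required n | Power at n = 71 |
|---|---|---|
| One-sided 5% | 71 | 0.805 |
| Two-sided 5% | 90 | 0.703 |

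The stated 71 is matched exactly, but only by the one-sided test. The gap from 71 to 90 is due to sidedness alone. The SD question plays no part in it.

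**Step 2: if 100 m is the SD of distance.** Assume equal SDs at T1 and T2 and a correlation r between them. Then

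SD of change = 100 × √(2(1 − r)), and the paired effect size = 30 / SD of change.

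For example, r = 0.7 gives 100 × √0.6 = 77.5 m and 30/77.5 = 0.387. The article gives no r, so a range is shown as an assumption.

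| Assumed r | SD of change (m) | Paired effect size | n, one-sided | n, two-sided |
|---|---|---|---|---|
| 0.3 | 118.3 | 0.254 | 98 | 125 |
| 0.4 | 109.5 | 0.274 | 84 | 107 |
| 0.5 | 100.0 | 0.300 | 71 | 90 |
| 0.6 | 89.4 | 0.335 | 57 | 72 |
| 0.7 | 77.5 | 0.387 | 43 | 55 |
| 0.8 | 63.2 | 0.474 | 29 | 37 |

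The two SDs coincide at r = 0.5. Two-sided, 71 is enough from about r = 0.605 upwards, that is, for an SD of change of about 89 m or less.

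**Step 3: consequence for the planned total.** The regression requirement gives the target: 92 × 1.25 = 115. Losing 25% of 115 leaves 115 × 0.75 = 86.25, about 86 patients. Two-sided power for 30 m with 86 pairs:

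| SD of change (m) | r, if 100 m is the SD of distance | Power at n = 86 |
|---|---|---|
| 118.3 | 0.3 | 0.64 |
| 100.0 | 0.5 | 0.79 |
| 89.4 | 0.6 | 0.87 |
| 77.5 | 0.7 | 0.94 |

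**The case against.** A reader might infer that the article divided by the wrong SD and that 71 is therefore an arithmetic error. The document does not support that. It never says that 100 m is the between-patient SD. The figure appears in a paragraph about paired differences, and heterogeneity could also justify a cautious SD of change, since patients may respond differently. Only the group's cited studies could settle this, and they are not part of the document. Even if 100 m is the SD of distance, the two SDs agree at r = 0.5, and above that value 100 m is conservative. Taking the upper end of 80 to 100 m is cautious as well. All of this stands, so the SD point is an unsupported input and does not prove that 71 is wrong.

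It can also be said that a journal article leaves such detail to the full protocol. That has force for the correlation. It does not cover a stated sample size that cannot be obtained from its own stated inputs without an undisclosed one-sided test.

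Finally, 71 does not drive recruitment, because the regression requirement is larger. The 25% drop-out covers the whole 21 months, so more than 86 patients may well have T2 data. Both statements are correct, and they limit the practical effect.

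**Conclusion.** The point holds in a limited form. From d = 0.3, 80% power and a 5% level, 71 data sets follow only from a one-sided test that the article does not declare. On a two-sided reading the requirement is 90, and 71 gives power of about 0.70. This part needs no assumption beyond the article's own inputs and a paired t-test.

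The second part is conditional. The 100 m is not shown to be an SD of change, so d = 0.3 is not justified as a paired effect size. If it is the SD of distance, the two-sided requirement lies between 125 (r = 0.3) and 37 (r = 0.8). Depending on r, 71 may be too few or more than enough.

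The planned total is not undermined. With about 86 patients remaining, two-sided power is about 0.79 at an SD of change of 100 m, just under the planned 80%.

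**What to change.** In the Sample Size Calculation section:

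1. State that the paired T1–T2 test is two-sided at 5%.
2. State whether 100 m is the SD of the change or of the distance.
3. If it is the SD of change, replace 71 by 90.
4. If it is the SD of distance, use the SD of change from the group's own cited studies. If those do not report it, use 100 × √(2(1 − r)), state the assumed r, and give the matching two-sided number (125, 107, 90, 72, 55 or 37 for r = 0.3 to 0.8). Drop the lower correlations only if data exclude them.
5. Add that about 86 patients after 25% drop-out give two-sided power of about 0.79 for 30 m at an SD of change of 100 m.

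The cost is one recalculation and a few sentences. The recruitment target of 115 need not change on this account.

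### The 71 data sets planned for the paired T1-T2 6MWT comparison are a one-sided result that the protocol never declares; a two-sided 5% test needs 90, and 71 pairs give about 70% power

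*Protocol article*

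**What the plan says.** The Sample Size Calculation section of the protocol article sizes two analyses in G*Power: a multiple regression (92 data sets) and a paired comparison of the 6MWT. On the paired comparison it says: "To detect the outcomes over time, differences between 2 dependent samples (T1 and T2) will be analyzed". The inputs follow. "The minimal clinically important difference between two measurement time points is 30 meters for the 6-minute-walking-distance". The SD is set at the upper end of an expected range of 80 to 100 m: "Assuming a standard deviation of 100 m (due to heterogeneity of the sample"). The result is "an expected effect size of d = 0.3, 71 data sets are required with a power of 80% and significance level of 5" per cent. The section then expects 25% drop-out and plans at least 115 patients.

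The Statistical Analysis section names the test for changes over time ("will be realized using the paired *T*-test or Wilcoxon-test") and the error level: "Bonferroni correction for multiple testing will be applied and statistical significance level will be set to *p* < 0.05". Neither section says whether tests are one-sided or two-sided.

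**The concern.** A 5% significance level given without a direction is normally read as two-sided, and 71 is too small for a two-sided paired t-test at d = 0.3. If the one-tailed option was used for the calculation and the analysis is then run two-sided, the stated 80% power does not belong to the planned test. The 6MWT is the article's primary outcome for physical performance, so this is the power statement that readers will rely on for the within-patient change. A figure of 71 also makes the sample look more comfortable than it is: 86 patients remaining after drop-out lie well above 71 but just below 90.

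**Working it through.** **Inputs, all from the Sample Size Calculation section unless noted**
- Difference to detect: 30 m
- SD: 100 m, so d = 30 / 100 = 0.3
- Power 80%, significance level 5%, direction not stated
- Stated requirement: 71 data sets
- Regression requirement: 92; drop-out 25%; total at least 115
- Test: paired t-test or Wilcoxon test (Statistical Analysis section)

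**Method.** Exact power of the paired t-test, as G*Power computes it: noncentral t with df = n - 1 and noncentrality d × √n. The critical value is the 95th percentile of t for a one-sided 5% test and the 97.5th percentile for a two-sided one.

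**Step 1: reproduce the stated figure**

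One-sided 5%:
- n = 70: noncentrality 0.3 × √70 = 2.510, critical t 1.667, power 79.97%
- n = 71: noncentrality 0.3 × √71 = 2.528, critical t 1.667, power 80.5%

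So 71 is exactly the smallest one-sided n. It is a correct one-tailed result.

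**Step 2: the same inputs, two-sided**
- n = 71: noncentrality 2.528, critical t 1.994, power 70.3%
- n = 89: noncentrality 2.830, critical t 1.987, power 79.9%
- n = 90: noncentrality 2.846, critical t 1.987, power 80.4%

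The two-sided requirement is 90. The normal approximation agrees closely: ((1.960 + 0.842) / 0.3)² = 87.2, rounded up to 88, against ((1.645 + 0.842) / 0.3)² = 68.7, rounded up to 69, one-sided. With SD 100 m, 71 pairs have 80% two-sided power for a change of 33.7 m, not for the 30 m the calculation is built on.

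**Step 3: does the Wilcoxon test explain 71?** No. Its relative efficiency is 3/π (about 0.955) under normality and 0.864 in the worst case. The requirements are then 74 and 82 one-sided, and 94 and 104 two-sided.

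**Step 4: what the planned sample delivers (two-sided 5%, d = 0.3, no multiplicity correction)**

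| Pairs | Where the number comes from | Power |
|---|---|---|
| 71 | stated requirement | 70.3% |
| 86 | 115 × 0.75 = 86.25 | 78.5% |
| 90 | two-sided requirement | 80.4% |
| 92 | regression requirement | 81.2% |
| 115 | all patients planned | 89.1% |

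**Step 5: which figure sets the total?** The regression's 92 reproduces (f² = 0.15, 5 predictors, power 80.4%). It is larger than both 71 and 90, and 92 × 1.25 = 115. Correcting 71 to 90 therefore leaves the total of 115 unchanged by the protocol's own method.

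**Step 6: what d = 0.3 assumes about the SD.** In a paired test d is the mean change divided by the SD of the change. If 100 m were instead the SD between patients at one time point, the SD of the change would be 100 × √(2(1 - r)), with r the correlation between T1 and T2. The article gives no r. As assumptions:
- r = 0.3: d = 0.254, two-sided n = 125
- r = 0.5: d = 0.300, two-sided n = 90
- r = 0.7: d = 0.387, two-sided n = 55

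**The case against.** The strongest reply is that the article never writes two-sided, so two-sidedness is an inference. The literature reviewed in the Introduction reports gains after rehabilitation, a directional hypothesis is conceivable, and 71 is a correct one-tailed result. That the regression was sized with an F test proves nothing, because an overall F test has no one-sided option. All of this stands. The defect is an undeclared one-sided calculation, and the 10-point loss of power holds for a two-sided analysis. It does not rescue the text: the article speaks of differences, sets an unqualified p < 0.05, and states no directional hypothesis.

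Second, 71 does not determine recruitment, and the T1-T2 comparison will probably have more than 71 pairs. The two measurements span an inpatient stay of at least 3 weeks, whereas the 25% drop-out is expected over 21 months. This also stands, and it limits the severity.

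Third, 100 m is the conservative end of the expected range; with an SD of 90 m the two-sided requirement is 73, and with 80 m it is 58. True, but the article fixes 100 m and d = 0.3, and the stated number must follow from those inputs.

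A reader might also infer that the study is underpowered at 6 and 12 months (T3, T4), because 86 is below 90. The documents do not support that as a finding. The protocol sets d = 0.3 for T1-T2 only and states no effect for later time points, so 78.5% there is only an illustration.

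**Conclusion.** The point holds as the correction of a stated figure. At d = 0.3, 80% power and a 5% level, 71 is the one-sided requirement. The two-sided requirement is 90, and 71 pairs give 70.3% two-sided power. This rests on reading an unqualified 5% level as two-sided and on taking 100 m as the SD of the within-patient change.

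It is a should-fix matter. A reader might infer that the study as a whole is too small or that the total of 115 is wrong because of this error. That does not follow: the regression's 92 sets the total, and T1-T2 power is about 89% with nearly complete data and 78.5% with 86 pairs. Both values are before the Bonferroni correction that the Statistical Analysis section announces, which would lower them by an amount that depends on the number of comparisons.

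**What to change.** In the Sample Size Calculation section:
1. Replace 71 with 90 and write two-sided 5%.
2. State that d = 0.3 takes 100 m as the SD of the within-patient change from T1 to T2.
3. Add the power that the planned sample delivers for T1-T2: about 89% if nearly all 115 patients have both measurements and about 78.5% if 86 remain, before any Bonferroni correction.
4. If power at T3 or T4 is quoted, label it as illustrative.

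If a one-sided test was truly intended, the text would be consistent only once that is declared and justified in both the Sample Size Calculation and the Statistical Analysis sections.

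The cost is a few words and one number. Because 90 is below the 92 that sets the total, no change to the planned 115 is asked for. Holding 90 pairs after a full 25% loss would take 90 / 0.75 = 120 patients, but the protocol does not set that target for T1-T2, and this point does not request it.
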